## Primary Outcome

The primary outcome is the proportion of stable ART patients receiving 3-month refills, defined as:

The number of stable patients given a 3-month refill in the previous month divided by the total number of stable patients seen in the last month.

Stable patients are defined as:

A patient active in ART care for more than 6 months and on first-line treatment as outlined in the Zambia Consolidated Guidelines (includes the following combinations **(1)** TDF + XTC + EFV, **(2)** TDF + XTC + LPV-r, **(3)** TDF + XTC + ATV-r, **(4)** TDF + XTC + NVP+, **(5)** AZT + 3TC + LPV-r, **(6)** ABC + 3TC + LPV-r, **(7)** ABC + 3TC + EFV).

Secondary outcomes include:

- Patient wait times based on the daily average wait time from entry into the clinic to medication delivery
- Compliance to quality improvement standard operating procedures
- Patient satisfaction and perceptions of quality of care
- Patient experiences with transition to multi-month refills
- Provider perspectives on process of implementing clinical efficiency and supply chain interviews and on barriers or challenges to providing multi-month refills
- Patient and provider perceptions on reliability of supply chain

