## *6.3 Study procedures*

### 6.3.1 Clinic efficiency and supply chain assessment

1. The first component of the study will be a detailed assessment of failures in clinic efficiency and supply chain. This will include, but not be limited to:
  - Patient flow assessment will be measured in each site over 2 days recording the patient wait times at each component of the clinic.
  - Patient exit interviews to receive information on their experience; what they think works well at the clinic and what does not work well.
  - Data collection at the pharmacy dispensing site to identify rationale for refill interval length.
  - Data from the ART register that identifies stable patients will be linked to the pharmacy dispensing data in order to determine the baseline proportion of stable patients receiving 3 month refills.
  - An assessment of supply chain reports, requisition forms and the flow of supply related reports and commodities.
  - Key informant interviews of facility, district and MSL staff to determine each member's experiences and cited challenges in the provision of ART care and 3-month refills in particular.

- An assessment of any available quality improvement checklist and standard operating procedures related to dispensing ARTs.

Data collection forms are attached as Annex 1 to 7.

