#### 6.3.4 Ethical considerations

Informed consent will be sought from each key informant or patient exit interview participant in accordance with IRB approval following an explanation of the study using a Plain Language Statement approved by the IRB. Study staff will clearly explain the rights of potential participants to decline to participate at any point without any negative consequence.

Both consent forms and patient information sheets are attached to this application as Annex 8 and 9 respectively. A minimal dataset summarising the outcomes from those approached for the Plain Language Statement will be recorded through a Screening Log.

Participant questionnaires approved by the IRB in electronic or paper format will be used to document patient wait times, information relating to the barriers/influences of being retained in ART care, patient and facility staff identified challenges regarding the provision of longer refills, and some socio-demographic indicators.

This study will be conducted according to Good Epidemiological Practises. Staff will be required to have undergone training in ethics and the management of study records according to Standard Operating Procedures.

The risks of this study relate only to access of identifiable information. As outlined above the study team will go to great lengths to ensure patient confidentiality is maintained. All staff will have been trained and committed to maintain confidentiality. Only unidentifiable records will be stored in a password protected database and any original Case Report Forms will be stored in a locked filing cabinet within a locked room at the Clinton Health Access Initiative Office in Lusaka.

The benefits of the study will be for improved efficiency measures being rolled out across all sites should the MOH decide that the intervention was successful.

No compensation will be provided to participants of surveys other than refreshments.

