### 6.5.1 Secondary analyses

Secondary analyses will consider the impact of the intervention by comparing mean and the variability of patient wait times and score of satisfaction between the intervention and control sites. We will run similar bivariable comparisons to examine how these factors may be associated with potential confounders. Then, paired t-tests will be used to examine the mean differences between the two groups for the variable of patient wait times and other secondary outcomes. Conditional multivariable analyses will be used to account for matched analyses as well as potential confounders. In addition, we will

describe compliance to the intervention and qualitative assessment on process successes and failures as well as patient and staff satisfaction.

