### DAILY PATIENT INFORMATION/CLINIC FLOW

| 1
ID | 2
ARRIVAL TIME OF PATIENT |     | 3
REGISTRATION TIME |     | 4
TIME AT TRIAGE |     | 4
CLINICAL ASSESSMENT TIME |     | 4
ART DISPENSED TIME |     |
|---------|------------------------------|-----|------------------------|-----|---------------------|-----|-------------------------------|-----|-------------------------|-----|
| Line    |                              | HRS |                        | HRS |                     | HRS |                               | HRS |                         | HRS |
| 1       |                              |     |                        |     |                     |     |                               |     |                         |     |
| 2       |                              |     |                        |     |                     |     |                               |     |                         |     |
| 3       |                              |     |                        |     |                     |     |                               |     |                         |     |
| 4       |                              |     |                        |     |                     |     |                               |     |                         |     |
| 5       |                              |     |                        |     |                     |     |                               |     |                         |     |
| 6       |                              |     |                        |     |                     |     |                               |     |                         |     |
| 7       |                              |     |                        |     |                     |     |                               |     |                         |     |
| 8       |                              |     |                        |     |                     |     |                               |     |                         |     |
| 9       |                              |     |                        |     |                     |     |                               |     |                         |     |
| 10      |                              |     |                        |     |                     |     |                               |     |                         |     |

|                                      |             |                  |                          |

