|     |                                                                                                       | Don't know |  | 99 | SKIP TO 4.6 |
| 4.8 | Please describe any changes that have happened in the care that you receive?                          |            |  |    |             |
| 4.9 | Did you receive ART drugs during this                                                                 | No         |  | 0  | SKIP        |

|      |                                                                                                                                              |                        |  |    |              |
|------|----------------------------------------------------------------------------------------------------------------------------------------------|------------------------|--|----|--------------|
|      | visit?                                                                                                                                       |                        |  |    | TO 4.8       |
|      |                                                                                                                                              | Yes                    |  | 1  |              |
|      |                                                                                                                                              | Don't know             |  | 99 | SKIP TO 4.8  |
| 4.10 | How many months of ART drugs did you receive?                                                                                                | Less than one month    |  | 0  | SKIP TO 4.10 |
|      |                                                                                                                                              | One month              |  | 1  |              |
|      |                                                                                                                                              | Two months             |  | 2  |              |
|      |                                                                                                                                              | Three months           |  | 3  |              |
|      |                                                                                                                                              | More than three months |  | 4  |              |

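### Wait time is undefined for patients who leave without drugs, and the flow form records neither when nor why they left, so any effect of such leaving on the comparison cannot be checked

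*Combined protocol and SAP*

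**What the plan says.** The first secondary outcome in section 6.1.3 is "Patient wait times based on the daily average wait time from entry into the clinic to medication delivery". The interval starts at arrival and can end only when drugs are handed over.

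The Patient Flow Data Collection Form (Annex 3) has one row per patient. It runs from "ARRIVAL TIME OF PATIENT" through registration, triage and "CLINICAL ASSESSMENT TIME" to "ART DISPENSED TIME". It has no column for time of leaving, for leaving without drugs, or for a reason. Section 6.3.1 says how the data arise: "Patient flow assessment will be measured in each site over 2 days recording the patient wait times at each component of the clinic".

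Section 6.5.1 plans "comparing mean and the variability of patient wait times" between intervention and control sites, then paired t-tests and conditional multivariable models. It does not say what happens to a row that has an arrival time but no dispensing time.

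Two other instruments might have filled the gap:

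- Section 6.3.4 says questionnaires "will be used to document patient wait times", but the annexed exit interview (Annex 7) has no field for the length of the wait.
- Exit item 4.9 asks "Did you receive ART drugs during this" visit. It belongs to a block that Annex 7 restricts to the endline survey and to facilities that received the intervention.

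**The concern.** Followed as written, the plan can compute a wait only for a patient who received drugs. That condition arises after randomisation, and the intervention is meant to change it: the synopsis describes an intervention to improve both clinic efficiency and ART supply. A mean taken over dispensed visits may therefore rest on differently selected patients in the two arms.

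The documents make wait-driven leaving plausible, though they do not measure it. Section 5.2 reports staff experience that long waits reduce retention, and the exit interview lists waiting time as a possible difficulty in receiving care. If patients with the longest waits are the likeliest to give up, and fewer give up where the intervention works, more of the long waits are counted in the intervention arm. The difference in means is then pulled towards zero. The planned comparison of variability would be affected too.

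Wait time is the secondary outcome closest to the ministry's question about congestion, and section 6.5.4 says the results will inform scale-up.

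**Working it through.** **No figure to reproduce.** The documents give no mean, SD, target difference or power for wait time, and no share of patients leaving without drugs. The first step is therefore textual and the second is an illustration.

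**Step 1: follow one undispensed patient through the plan.**

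- Outcome definition (section 6.1.3): there is no end point, so no wait.
- Flow form (Annex 3): arrival and some intermediate times may be present and the dispensing time is blank. The blank cannot separate giving up, a stock-out, no refill due, still waiting at close, or a missed entry.
- Analysis (section 6.5.1): no rule.
- Exit interview (Annex 7): no wait length. Drug receipt is asked in one arm only and at endline only.

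Nothing recorded shows how long the patient waited before leaving, or why the patient left.

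**Step 2: how much could it matter?** All inputs here are assumptions.

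- Waits are lognormal, with true means of 240 minutes (control) and 200 minutes (intervention). The SD is 100 at a mean of 240, and the same coefficient of variation, 100/240 = 0.42, applies in both arms.
- Each patient has a patience time, lognormal with coefficient of variation 0.4, with the same distribution in both arms. A patient leaves undispensed if the wait exceeds it.
- Median patience is set so that a chosen share leaves in control. The intervention share then follows.

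Simulation with 2,000,000 patients per arm gave a true difference of 39.9 minutes, and these results for dispensed patients only:

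| Leave, control | Leave, intervention | Mean, control | Mean, intervention | Difference | Loss against 39.9 |
|---|---|---|---|---|---|
| 2% | 0.9% | 235.4 | 198.2 | 37.3 | 2.6 min (7%) |
| 5% | 2.4% | 230.6 | 195.6 | 34.9 | 5.0 min (13%) |
| 10% | 5.4% | 224.0 | 191.8 | 32.2 | 7.7 min (19%) |
| 20% | 12.1% | 213.1 | 184.6 | 28.4 | 11.5 min (29%) |

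(Differences were taken before rounding.)

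**Closed-form check of the 10% row.** The log-scale variances are σw² = ln(1 + (100/240)²) = 0.160 for waits and σp² = ln(1 + 0.4²) = 0.148 for patience, so s = √(0.160 + 0.148) = 0.555. With a = Φ⁻¹(share dispensed), the mean among dispensed patients is true mean × Φ(a − σw²/s) / Φ(a).

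- Control: a = 1.282, so 240 × Φ(1.282 − 0.288) / 0.900 = 240 × 0.8397 / 0.900 = 223.9.
- Intervention: a = 1.282 + ln(240/200)/0.555 = 1.610, so Φ(a) = 0.9463 and 5.4% leave. The mean is 200 × Φ(1.610 − 0.288) / 0.9463 = 200 × 0.9068 / 0.9463 = 191.7.
- Difference: 223.9 − 191.7 = 32.2, in agreement with the simulation.

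**Leaving unrelated to the wait.** With 5%, 10% or 20% leaving in control and half that in intervention, the difference among dispensed patients is 39.9 to 40.0 minutes. There is no bias.

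**Extreme case, for comparison.** Suppose waits are normal with SD 80, and exactly the longest 10% (control) and 3% (intervention) are lost. The mean with the top fraction p removed is μ − SD × φ(z₁₋ₚ)/(1 − p). This gives 240 − 80 × 0.1755/0.90 = 224.4 and 200 − 80 × 0.068/0.97 = 194.4, so a true 40 minutes reads as 30.0. It requires a perfect link between wait and leaving.

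**The case against.** A reader might infer more than this: that the plan discards undispensed patients, that the longest waits disappear from the control arm, and that a 40-minute gain would read as 30. The documents do not support that reading.

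- **The plan is silent.** Exclusion is the natural default under the definition, but no section states it.
- **No leave rate is given for either arm.** Facilities are pair-matched and randomised (section 6.1). Without an intervention effect, leaving should be similar by arm, so wait-driven leaving produces no systematic false benefit. In the scenarios examined it only weakens a real effect.
- **Item 4.9 is weak evidence.** A negative answer also covers visits with no refill due. The item is asked in intervention facilities only, of a separate sample of every tenth patient leaving. It shows neither walk-outs nor a difference between arms.
- **Departures differ in kind.** Leaving because of a stock-out depends on stock and need not follow a long wait. When leaving is unrelated to the wait, the bias is nil.
- **The 30-minute figure is arithmetically right but a worst case.** It removes exactly the longest waits.
- **The form already holds something.** A blank dispensing time beside an arrival time gives a crude count of undispensed visits in both arms, and the intermediate times may survive.

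All of this stands and limits the claim. What remains is that a blank cannot be interpreted: without time and reason for leaving, harmless and harmful missingness cannot be told apart afterwards.

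**Conclusion.** The gap is real and can be read directly from the outcome definition, the form and the analysis section. A patient who leaves without drugs has no defined wait, no recorded departure and no analysis rule.

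The bias is conditional. It needs leaving to be driven by the wait and to be less common under the intervention. Under the assumed inputs, the between-arm difference then shrinks by about 7% with 2% leaving in control and by about 29% with 20% leaving. It shrinks by about zero if leaving is unrelated to the wait. Neither the presence nor the size of the bias follows from the documents.

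The point concerns a secondary outcome. The primary outcome comes from linked register and pharmacy data (section 6.3.1), not from the flow form. This is a low-cost improvement and not a flaw that threatens the study.

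**What to change.** 1. Add two fields to the Patient Flow Data Collection Form, completed identically in both arms and at each round of flow observation: time left the clinic, and a visit-outcome code (dispensed; left while waiting; left because of stock-out; no refill due; still waiting at close).
2. Report, by arm and round, the share of refill-seeking visits that end without drugs. Visits with no refill due do not belong in that denominator.
3. In section 6.5.1, state that the planned mean applies to dispensed visits. Add a sensitivity analysis of all refill-seeking visits that either counts undispensed patients as exceeding their observed time (for example, through a clinic-day median) or treats stock-out departure as a competing event. Compare the results between matched pairs, as already planned for the means.

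Do not simply censor every undispensed patient at departure in a Kaplan-Meier analysis. That treats a patient who left because of a stock-out as still due drugs that day. If such departures are commoner in control clinics, it could lengthen their estimated waits and favour the intervention.

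The cost is slightly more recording per patient, on a form already completed per patient over 2 days at each site, and one added analysis. Departure times not recorded during observation are unlikely to be recoverable later.

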## *6.2 Eligibility for recruitment*

### 6.1.4 Inclusion criteria

Facilities that have agreed to participate and have the potential to increase the proportion of stable patients on 3-month refills by 20% (currently have less than 80% of stable patients on 3 month refills).

Adult ART patients aged 18 years and over will be eligible for the exit interview.

### 6.1.5 Exclusion criteria

Facilities will be excluded if they are currently participating in research that may interfere with our primary or secondary outcomes.

## *6.3 Study procedures*

### 6.3.1 Clinic efficiency and supply chain assessment

1. The first component of the study will be a detailed assessment of failures in clinic efficiency and supply chain. This will include, but not be limited to:
  - Patient flow assessment will be measured in each site over 2 days recording the patient wait times at each component of the clinic.
  - Patient exit interviews to receive information on their experience; what they think works well at the clinic and what does not work well.
  - Data collection at the pharmacy dispensing site to identify rationale for refill interval length.
  - Data from the ART register that identifies stable patients will be linked to the pharmacy dispensing data in order to determine the baseline proportion of stable patients receiving 3 month refills.
  - An assessment of supply chain reports, requisition forms and the flow of supply related reports and commodities.
  - Key informant interviews of facility, district and MSL staff to determine each member's experiences and cited challenges in the provision of ART care and 3-month refills in particular.

- An assessment of any available quality improvement checklist and standard operating procedures related to dispensing ARTs.

Data collection forms are attached as Annex 1 to 7.

#### 6.3.2 Intervention design

The design of the intervention will be informed by the above assessment. In particular, critical process failures will be identified and an intervention designed to resolve the issue. A stakeholder meeting will take place and involve all relevant parties including Facility in-charges, District Pharmacists and ART Coordinators, MSL staff responsible for ART supply, and collaborators such as CIDRZ. The purpose of this stakeholder meeting is to ensure that there is buy-in and ownership of the intervention from all relevant stakeholders.

#### 6.3.3 Assessment of the impact of the intervention

Based on the randomized pair-matched study design, ongoing assessments will measure process and outcome indicators (outlined below).

#### 6.3.4 Ethical considerations

Informed consent will be sought from each key informant or patient exit interview participant in accordance with IRB approval following an explanation of the study using a Plain Language Statement approved by the IRB. Study staff will clearly explain the rights of potential participants to decline to participate at any point without any negative consequence.

Both consent forms and patient information sheets are attached to this application as Annex 8 and 9 respectively. A minimal dataset summarising the outcomes from those approached for the Plain Language Statement will be recorded through a Screening Log.

Participant questionnaires approved by the IRB in electronic or paper format will be used to document patient wait times, information relating to the barriers/influences of being retained in ART care, patient and facility staff identified challenges regarding the provision of longer refills, and some socio-demographic indicators.

This study will be conducted according to Good Epidemiological Practises. Staff will be required to have undergone training in ethics and the management of study records according to Standard Operating Procedures.

The risks of this study relate only to access of identifiable information. As outlined above the study team will go to great lengths to ensure patient confidentiality is maintained. All staff will have been trained and committed to maintain confidentiality. Only unidentifiable records will be stored in a password protected database and any original Case Report Forms will be stored in a locked filing cabinet within a locked room at the Clinton Health Access Initiative Office in Lusaka.

The benefits of the study will be for improved efficiency measures being rolled out across all sites should the MOH decide that the intervention was successful.

No compensation will be provided to participants of surveys other than refreshments.

